### Randomization

All the participants will be randomly assigned to GGOC-AD (intervention) or GGN-AD (control) groups (allocation 1:1) with the randomizer.org platform (no block randomization). It will take place prior to the T1 assessment and will be conducted by a researcher not involved in the assessment and intervention procedure.

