Figure 1 depicts the trial design and times of assessment. Students will be recruited from public schools in the metropolitan area of Valencia (Spain). Researchers will invite different schools to participate in the study. After the education center agrees to participate, members of the research group will meet students in the designated classroom, provide information about the study, and invite them to participate. Students will then receive a sheet with information about the study and the informed consent for parents or guardians and the student. Finally, participants that explicitly agree to participate, provide the informed written consent, and meet the inclusion criteria will be randomized in two groups: the intervention group that will use GGOC-AD and the control group that will use the GGN-AD module. On weekdays, students will complete the app during school hours at a pre-arranged time with the education center in order to interfere as little as possible. At least two members of the research group will be available to assist in the assessment sessions (T1-T3) and monitor the use of the app in order to promote participants’ retention. Students will be asked to complete the app at home during the weekend. As shown in Fig. 1, on the first day of the study, participants will be requested to complete the baseline assessment measures (T1, pre-treatment) and download the GGtude platform app using their personal mobile device. It will be freely available from the App Store or Google Play. The intervention group will access the GGOC-AD module of said app and the control group will use the GGN-AD module. Users will carry out cognitive training for 14 consecutive days, completing approximately three levels per day. On the day that they finish the app (day 14), participants will be instructed to complete the assessment instruments again (T2, post-treatment). Finally, a one-month follow-up evaluation will be conducted (T3). Both groups will complete the outcome measures and the app at about the same time, using their personal mobile device. At all-time assessments, questionnaires will be completed by Lime Survey software in a designated classroom.

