### Primary and secondary outcome measures

All measures will be completed at pre-, post- and follow-up assessment. Participants will also complete a sociodemographic data sheet (*see additional measures*). The primary outcomes measures will be:

*Obsessive Compulsive Inventory - Child Version* (OCI-R-CV) [27]. The OCI-R-CV is a self-report instrument that assesses the discomfort associated with obsessive-compulsive symptoms in children and adolescents between 8 and 18 years old. It consists of 21 items with a 3-point Likert scale (from 0 = “never” to 2 = “always”). The total score and the six subscales (Doubting, Obsession, Hoarding, Washing/Checking, Ordering, and Neutralizing) will be used in this study. The Spanish validation of the OCI-R-CV shows good psychometric properties [28].*Obsessive Beliefs Questionnaire - Child Version* (OBQ-CV) [29]. The OBQ-CV is a self-report questionnaire that assesses obsessive beliefs through 44 items with a 5-point Likert scale (from 0 = “strongly disagree” to 4 = “strongly agree”). In this study, we will consider the three subscales: a) Responsibility and threat estimation, b) Perfectionism and intolerance of uncertainty, and c) Importance and need to control thoughts, and the OBQ-CV total score. The Spanish adaptation presents good psychometric properties [30].

The secondary outcome measures will be as follows:

*The Patient Health Questionnaire for Depression and Anxiety* (PHQ-4) [31, 32]. This is a brief-screening to assess anxiety and depression symptoms. It is composed of 4 items evaluated with a 4-point Likert scale (from 0 = “never” to 3 = “almost every day”). The total score and the two subscales (anxiety and depression) will be used in this study. The Spanish validation shows good psychometric properties [33].*Single-Item Self-Esteem Scale* (SISE) [34]. The SISE is a self-report measure that determines the extent to which the sentence “I have a high self-esteem” describes participants on a 9-point scale, ranging from 1 (“not very true for me”) to 9 (“very true for me”). In this study, the SISE will be used as a self-esteem score, in accordance with the reliability and criterion validity reported by Robins et al. [34].

Additional measures:

*Sociodemographic data sheet:* The data required will be the following: age, gender, data about their school center (academic year, class group, and school center).

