### Statistical analyses and sample size

Analyses will be performed using the free software R. The effect of the intervention on primary and secondary measures over time will be appraised using a generalised linear mixed model (GLMM), and, specifically, a linear multiple regression model where time (T1, T2 and T3) and group (experimental and control) are the independent variables whereas the primary and secondary outcome measures are the dependant variables. To avoid overly optimistic estimates of the effectiveness of the experiment, an ITT (intention to treat) approach will be used, using the method of multivariate imputation by chained equations algorithm (MICE). Descriptive statistics such as means, standard deviations, and frequencies will be also calculated.

The sample size of the study has been estimated a priori using G-power 3 [35] based on the formula provided by Cohen [36]. It was revealed that a sample of at least 55 participants will need to be recruited to accomplish a power study of .805 at alpha = .05 and a medium size effect (.15). Considering the dropout rates in previous studies in our context [21], we will invite approximately 200 individuals to participate in the current study.

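### Randomisation precedes the self-reported T1 baseline with no stated concealment until T1 is submitted, which leaves a risk of response bias and makes T1 losses post-randomisation losses

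*Protocol article*

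**What the plan says.** All references are to the protocol article.

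- **Order.** The Randomization section states: "It will take place prior to the T1 assessment". It gives the task to a researcher who has no part in assessment or intervention. The Study design and procedure section agrees on the order. Students who agree to take part, "provide the informed written consent, and meet the inclusion criteria will be randomized in two groups"; a completed baseline is not among the conditions. On the first study day, "participants will be requested to complete the baseline assessment measures (T1, pre-treatment) and download the GGtude platform app using their personal mobile device".
- **Staff.** The same section has at least two research-group members in attendance to help at all three assessments, and gives them the task of overseeing app use.
- **Outcomes.** Both primary instruments are self-report. For the beliefs measure: "The OBQ-CV is a self-report questionnaire that assesses obsessive beliefs through 44 items". Questionnaires are completed electronically in a classroom.
- **Analysis.** Under Statistical analyses and sample size, "time (T1, T2 and T3) and group (experimental and control) are the independent variables". An intention-to-treat approach with multiple imputation by chained equations is planned.
- **Control questions.** Under Data management, anyone who answers the two attention checks inadequately is removed from the database. The checks are included at every assessment, so T1 counts.

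**The concern.** A baseline is protected from the allocation when it is recorded before the allocation exists, or at least before anyone who can affect the answers knows it. Here the allocation already exists when T1 is completed. The only stated safeguard concerns who performs the randomisation, not when the result is disclosed or to whom.

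Two things are at stake.

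1. **Response bias at T1.** The questionnaires are self-report, T1 and the app download fall on the same day, and the staff who assist at T1 also oversee modules whose content plainly differs between arms. If the arm is known before T1 is finished, answers could differ by arm for reasons other than chance. Because T1 is a level of time in the model, that difference passes into the estimated change.
2. **Losses at T1.** A student who misses T1, or fails its control questions, has already been randomised. Had T1 come first, the same student would simply not have been randomised.

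**Working it through.** **Order of events.** The two sections give one consistent sequence: consent and eligibility, randomisation, T1, app download, module use. No part of the article reverses it. T1 is therefore post-randomisation but pre-exposure.

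**The plan's own figure.** The article gives N = 55, power .805, alpha .05 and effect size .15. Reading .15 as Cohen's f² for one tested regression coefficient, the noncentrality is N × f² = 55 × 0.15 = 8.25. The noncentral F then gives power 0.8051 with one predictor in the model (0.8048 with two, 0.8045 with three), and 55 is the smallest N that reaches 0.80. The figure reproduces. It does not depend on when randomisation takes place, so moving randomisation leaves it unchanged.

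**What a T1 shift would do.** The article gives no size for any shift, so everything here is assumed: a true effect of zero, 27 per arm (about 55/2), T1-T2 correlation ρ between 0.5 and 0.8, equal SDs, a shift s (in SD units) in one arm's T1 mean caused by knowing the arm, and the effect read as the between-arm difference in change from T1.

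- Bias of the change contrast = s in absolute size. Its sign depends on which arm shifts and in which direction, and the article gives no basis for either.
- Standard error = √(2(1−ρ)) × √(2/n).
- Type I error = 1 − Φ(1.96 − s/SE) + Φ(−1.96 − s/SE).

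Worked case, s = 0.2, ρ = 0.5, n = 27: SE = 1 × √(2/27) = 0.272; s/SE = 0.735; type I error = 0.114. With ρ = 0.8: SE = 0.632 × 0.272 = 0.172; s/SE = 1.162; type I error = 0.213.

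| Assumed shift s | Bias in change (SD) | Type I error, ρ = 0.5 to 0.8 |
|---|---|---|
| 0 | 0 | 0.05 |
| 0.1 | 0.1 | 0.07 to 0.09 |
| 0.2 | 0.2 | 0.11 to 0.21 |
| 0.3 | 0.3 | 0.20 to 0.41 |

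A larger sample does not help, because the bias stays while the standard error shrinks. About 200 students are to be invited. At 100 per arm, which would require all of them to take part, s = 0.2 gives 0.29 to 0.61. If the model adjusted for T1 as a covariate, which the article does not describe, the bias would be ρ × s and the corresponding type I error at 27 per arm for s = 0.2 would be 0.07 to 0.17.

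**What the T1 losses do.** These need no unblinding. A student absent at T1 belongs to the randomised set, and the baseline would have to be imputed. A student who fails the T1 control questions is removed after randomisation, so the analysed set is no longer everyone randomised. If the arm is unknown at T1, failure does not depend on arm: participants are lost, but the contrast is not biased. If the arm is known, even that protection goes.

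**The case against.** The strongest reply is that the order of allocation does not by itself bias a baseline; knowledge of the arm does. The article nowhere says the arm is disclosed before T1. Randomisation is done by someone outside assessment and intervention, T1 is listed before the download and module access, and both arms use the same app with similar structure, so the content that distinguishes them appears only on use. Staff assist but do not rate outcomes. The time of disclosure may be set out in a fuller protocol. All of this stands, and it limits the point to a risk. It does not remove the point, because randomising before baseline is a stated choice, not an omitted detail, and nothing described requires it.

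Three stronger readings are tempting and are not supported.

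- **That T1 is biased.** The documents show only that it could be.
- **That the bias can be put as a share of the expected effect.** The article gives no size for a shift and no standardised mean difference. Converting f² = .15 to a balanced two-group difference gives d = 2√.15 = 0.77, against which an assumed 0.1 to 0.2 SD shift is 13% to 26%. The numerator is still invented, so this percentage is not a finding.
- **That students who fail the T1 control questions enter the intention-to-treat set without a baseline.** Under Data management they are removed. Only students absent at T1 are in that position, and imputation is planned for missing data.

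**Conclusion.** The point holds as a design weakness that is easy to avoid. Randomisation before T1 is explicit, and the article states no concealment of the arm from students or attending staff until T1 is submitted. Whether T1 answers are affected depends on knowledge of the arm, which the article does not settle. The type I error figures show sensitivity under assumed shifts and correlations, and the rate stays at 0.05 if there is no shift.

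The second part rests on no assumption about unblinding: absences at T1 and failed T1 control questions fall after randomisation, and removing the latter group is at odds with the intention-to-treat statement. The article gives no rate for either loss, so their size is unknown. The margin in the stated sample size is thin, since 55 is the smallest N reaching 0.80, although inviting about 200 may absorb some losses.

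**What to change.** Draw the allocation only after T1 has been submitted and its control questions passed, for example class by class once T1 is locked, or on the next school day. Give access to the module after that, and define the intention-to-treat set as all students so randomised. This removes the response-bias risk, the missing baselines and the T1 exclusions together.

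If that is not practicable, the minimum is to state that the allocation is withheld from students and attending staff until T1 is locked. This removes the response-bias risk but leaves the T1 exclusions and missing baselines.

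The cost is a small logistical step between T1 and module access: the independent researcher, or a prepared release procedure, must be available around each school's T1 session. The T1 control questions also become a pre-randomisation screen and must be listed with the inclusion criteria. The sample size is unaffected. Removals for failed control questions at T2 and T3 are a separate problem that this change does not cure.

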### Data management

Data will be collected and managed in line with the Ethics Committee of Research in Humans of Universitat de Valènica. Participants will access the questionnaires using a unique personal identification number (ID), created beforehand. It is a code that ensures anonymity and does not allow participants to be identified. Their ID will be used to match the collected data. No other personal data is requested. Data from the questionnaires will be stored on a secure server of the Universitat de Valènica. In addition, persons who do not adequately answer the two control questions (e.g., “In this question, please check “always”) included in the questionnaires at each evaluation time will be eliminated from the data base.

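### Deleting students who fail the control questions is a post-randomisation exclusion and contradicts the stated intention-to-treat analysis

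*Protocol article*

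**What the plan says.** Three statements in the Methods of the protocol article bear on this.

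- **Randomization:** all participants are allocated 1:1, and of the timing the article says "It will take place prior to the T1 assessment".
- **Data management:** the rule concerns "persons who do not adequately answer the two control questions"; these questions are "included in the questionnaires at each evaluation time will be eliminated from the data base".
- **Statistical analyses and sample size:** "an ITT (intention to treat) approach will be used", with missing values handled by multivariate imputation by chained equations (MICE). The stated purpose is "To avoid overly optimistic estimates of the effectiveness of the experiment".

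There are three waves: "All measures will be completed at pre-, post- and follow-up assessment". Passing the control questions is not among the inclusion criteria under Participants. The article does not limit the deletion to the failed wave, and it does not say that deleted students remain in the intention-to-treat set.

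**The concern.** Attention checks are reasonable in a long self-report battery completed by adolescents. The difficulty is what the plan does with a failure. It removes the person, and it does so after allocation. An intention-to-treat analysis keeps everyone in the group to which they were randomised, and MICE fills gaps for people who are still in the data set. Neither is possible for someone who has been eliminated from it.

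The T2 and T3 checks matter most. By then one arm has spent 14 days on belief statements and the other 14 days on general-knowledge items, so attention at those waves is a post-treatment variable. If it differs by arm and is related to outcome, the students who remain are no longer a randomised comparison. Valid data may also be lost: if one failure is enough, a student with good T1 and T2 questionnaires who fails at T3 loses all three.

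**Working it through.** **1. The sequence and the possible readings**

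The order of events is allocation, T1, 14 days of module use, T2, then T3 one month later. Every control question is therefore answered after allocation, including those at T1. The deletion sentence can be read in three ways:

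| Reading | What is removed | Compatible with intention to treat plus MICE? |
|---|---|---|
| Failure at any one wave | The student, with valid data from other waves | No |
| Failure at all three waves | The student | No |
| Only the failed wave's responses | One questionnaire | Yes, but the text does not say this: it speaks of persons leaving the database |

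Both readings that follow the wording conflict with the analysis statement.

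**2. The plan's own figure**

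Inputs from Statistical analyses and sample size: N = 55, power .805, alpha .05, effect .15, which I read as Cohen's f². For one tested coefficient in a linear regression, the noncentrality is λ = f² × N = 0.15 × 55 = 8.25. With 1 or 2 predictors in total, the denominator degrees of freedom are 53 or 52, and power is 0.8051 or 0.8048. N = 55 is the smallest N that reaches .80. The stated figure reproduces and is not in dispute.

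**3. How many students the rule could remove (illustration)**

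The article gives no failure rate. Assume a rate q per wave, independent across three waves. On the any-wave reading, the share deleted is 1 − (1 − q)³. Apply this to 55 randomised students, round down, and use the power formula with two predictors:

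| Assumed q | Share deleted | Left of 55 | Power | Randomised so that 55 remain: 55/(1 − q)³ |
|---|---|---|---|---|
| 1% | 3.0% | 53 | 0.79 | 57 |
| 2% | 5.9% | 51 | 0.77 | 59 |
| 5% | 14.3% | 47 | 0.74 | 65 |
| 10% | 27.1% | 40 | 0.66 | 76 |

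On the all-waves reading the share is far smaller. Under independence it is q³, for example 0.10³ = 0.001. If the same students always fail, it can rise to at most q.

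**4. How far the comparison could shift (illustration)**

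Assume no true effect, an outcome with SD 1 on which higher is worse, and a latent tendency to fail that correlates 0.3 with the outcome. If a share q of an arm is deleted in total, the mean of those retained moves by −0.3 × φ(z)/(1 − q). Here φ is the standard normal density and z the point with upper tail area q.

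- q = 5%: 0.3 × 0.1031/0.95 = 0.033
- q = 10%: 0.3 × 0.1755/0.90 = 0.059
- q = 20%: 0.3 × 0.2800/0.80 = 0.105

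The bias in the arm difference is then:

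- 5% v 5%: 0
- 10% v 5%: 0.059 − 0.033 ≈ 0.03 SD
- 20% v 5%: 0.105 − 0.033 ≈ 0.07 SD

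A simulation with 2,000,000 draws gave 0.000, 0.026 and 0.073.

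For scale, f² = .15 for a balanced two-group contrast corresponds to d = 2 × √0.15 ≈ 0.77. A shift of 0.03 to 0.07 SD is therefore about 4% to 9% of the planned effect. The arm with more deletions looks better. If that is the intervention arm, the app is flattered; if it is the control arm, the app is disadvantaged.

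**The case against.** Several points on the other side are sound.

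- **Ambiguity.** The phrase about each evaluation time grammatically says where the control questions sit, not when a failure triggers deletion. A reader might infer that one failure at T3 certainly erases a student's T1 and T2 data. The text allows that but does not establish it. The ambiguity does not remove the conflict, because the all-waves reading also deletes randomised students. If only the failed wave was meant, the sentence still has to be rewritten.
- **Power.** A reader might infer that the trial will fall below its planned power. The article does not support this. It calls 55 a minimum and plans to invite about 200 because of dropout, and it does not say whether 55 is counted before or after losses. The table above is arithmetic on assumed rates, not a forecast. Extra recruitment, however, does not repair selection.
- **Direction.** A reader might also infer that the rule inflates the app's benefit, since engaged students are kept. Nothing in the article shows which arm would lose more students, so the bias could run either way.
- **Design safeguards.** The control module has a similar structure and the same number of levels. Both arms complete the measures at about the same time in a classroom, with researchers present. T1 precedes module use, so T1 failures are unlikely to depend on treatment. These features make a large difference in failure between arms less likely, but they do not exclude one at T2 or T3.
- **Condensed article.** Details may be left to a fuller plan. But the objection is not to a missing detail: the article states a rule that its own analysis principle forbids.

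**Conclusion.** The point stands as a contradiction in the text. The article cannot both eliminate randomised students from the database and analyse by intention to treat with imputation. This holds on the any-wave and all-waves readings alike and needs no assumed number.

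The consequence for the results is a possible bias of unknown size and direction. It is about zero if failure is equal across arms and related to outcome in the same way in each. It is about 0.03 to 0.07 SD under the assumed correlation of 0.3 and failure of 10% or 20% against 5%. That is small beside the planned effect, but it is avoidable. The documents do not support a claim that the trial is underpowered or that its result will favour the app.

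**What to change.** Reword the sentence under Data management along these lines: *All randomised students are analysed in their assigned group. If the control questions at a wave are failed, the questionnaire scores from that wave only are set to missing and handled by the planned MICE or mixed model.*

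Report the number of failures by arm and wave, and add one sensitivity analysis that uses the scores as recorded. Both can sit in the statistical analysis plan.

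The cost is a sentence and slightly more imputation. The imputation relies on missing at random, which may not hold fully if inattention is related to unobserved outcome. The change therefore reduces the selection problem without necessarily removing it, and the sensitivity analysis shows how much the handling matters. Screening on the control questions at T1 before allocation is not needed, and it would change the planned sequence, in which randomisation comes first.
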